### Premature Withdrawal of Patients from Study

Patients are free to withdraw consent and discontinue participation at any time without penalty and are not obliged to give a reason. Patients may be withdrawn/removed, if necessary, to protect their health or the integrity of the study. The Investigator also has the right to withdraw patients from the study in the event of intercurrent illness, adverse events, treatment failures, protocol violations, administrative, or other reasons. When a patient withdraws from the study, all safety data normally required at the completion of the study will be obtained, where possible. All details available will be reported and recorded for any patient that withdraws or is removed from the study.

If the reason for removal of a patient from the study is an adverse event, intercurrent illness, or an abnormal laboratory value, the principal specific event or test will also be recorded on the case report form (CRF).

CRFs are required for all patients who receive study medication, even if they subsequently withdraw from the study before all assessments are completed. All sections of the CRF, up to the time of withdrawal, are to be completed. Efforts should be made to obtain complete information regarding the tolerability and safety of the test drug. This means that asking for and recording Adverse Events should continue whenever possible. Patients who withdraw from the trial will not be replaced.

All patients who withdraw early from the study but have received all days of study medication will be included in the analysis of effectiveness.

All patients who withdraw from the study but receive at least one dose of study medication will be included in the analysis of safety.

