## Criteria for Discontinuation of Patient Study Drug and for Study Termination

A patient’s study drug will be discontinued for

1) any patient developing severe dengue based on WHO criteria or

2) any patient developing grade 3 severity diarrhoea

The study will be terminated at any time that the Data Safety and Monitoring Board members conclude that:

1) Clear and significant harm is noticed in the treatment;

2) ≥30% serious adverse reactions occur in the treatment arm that are possibly, probably or definitely related to study drug;

3) ≥30% patients develop severe dengue based on WHO criteria;

4) ≥30% patients develop grade 3 severity diarrhoea;

5) The drop out rate is too high (>30%).

Figure 2 Flowchart of patients’ activities

Placebo

(N = 25)

Celgosivir

(N = 25)

Drug administration

Drug administration

Daily assessment

Daily assessment

Return to IMU for assessment

Return to IMU for assessment

Visit to polyclinic or GP/ED of NUH or SGH

Assessment of high probability of dengue infection

Fever ≥38° of ≤ 48 hr duration

≥2 symptoms of dengue fever

Positive NS1 strip assay

Others

Referral to IMU for screening of other inclusion & exclusion criteria

Written inform consent

Baseline assessment

Randomization

Discharge

End of Study

Day 5

Day 1

Day 1 to Day 5

Days 7, 10, 15

Day 15

Prior to Day 1

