# Statistical Considerations

## Sample size calculation

To achieve 80% power to detect a difference of one log viremia reduction between the celgosivir treated group and the placebo group, assuming a standard deviation of one log, a sample size of 14 for each group (28 total) is required for a 5% one-sided type I error. With a sample size of 25 in each group (50 total), we are able to detect a difference of 0.7 log viremia reduction at a standard deviation of one log (equivalently a one log reduction at a standard deviation of 1.4 log) at 80% power.

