## Statistical analysis

A detailed statistical analysis plan will be prepared prior to unblinding.

General

Continuous variables will be summarized using mean and standard deviation. Categorical variables will be summarized by frequency and percentage. Percentages will be rounded to one decimal place and, therefore, may not always add up to 100. All statistical tests will be set at a 5% level of significance. All confidence intervals will be 95% and two-sided. Statistical analyses will be performed using SAS version 9.3.

Demographic and baseline characteristics

Descriptive statistics will be used to summarize demographics and baseline information and to assess balance between the two groups (mean, standard deviation, minimum, maximum, and median for continuous variables; frequency and percent for categorical variables).

Analysis population

Statistical analysis for efficacy data will be carried out on an intention-to-treat (ITT) basis. An ITT set is defined as all patients who signed the informed consent form for the study enrollment and obtained an enrollment number. The treatment group of patients in the ITT set is the planned treatment group, i.e., according to the randomization list planned prior to the study commencement.

Statistical analysis for safety data will be carried out on an as-treated basis. An as-treated set is defined as all subjects who signed the informed consent form for the study enrollment and obtained an enrollment number. The treatment group of patients in the as-treated set is according to the treatment actually received.

Primary outcome

The primary outcomes include the mean of virological log reduction at Day 2, Day 3 and Day 4 and fever AUC above baseline. The virological log reduction of each patient will be measured at Day 2, Day 3 and Day 4 when they are inpatients. The mean of these three measurements will be computed for each patient, and then be compared between the two groups by a two-sample, one-sided t-test. The body temperature of each patient will be measured at baseline and from Day 1 to Day 5, and a curve of the temperature will be plotted. The area under this curve but above the baseline value will be computed for each patient, and then be compared between the two groups by a two-sample, one-sided t-test.

Secondary outcomes

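### The primary virological t-test on a three-day mean has no value for an ITT patient missing Day 2, 3 or 4; a repeated-measures model would use the observed days at little cost

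*Protocol*

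**What the plan says.** Section 6.2 (Primary outcome) fixes the virological analysis in three steps. The values come from three inpatient days: "The virological log reduction of each patient will be measured at Day 2, Day 3 and Day 4 when they are inpatients". They are reduced to one number: "The mean of these three measurements will be computed for each patient". These numbers are "then be compared between the two groups by a two-sample, one-sided t-test".

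The same section sets the population: "Statistical analysis for efficacy data will be carried out on an intention-to-treat (ITT) basis". It gives a rule for a missing reference value for hemoconcentration, a secondary outcome, but none for a missing Day 2, 3 or 4 viral load. It also says that a detailed SAP will follow before unblinding.

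Section 3.2.3 says "Patients who withdraw from the trial will not be replaced". It states that patients who leave early but took drug on every treatment day count in the effectiveness analysis. It says nothing about other early leavers. Section 5.1 asks patients who stop drug to stay on the full assessment schedule.

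**The concern.** A log reduction is a cumulative fall from baseline. In a self-limiting infection it should grow from Day 2 to Day 4, so the three days are not interchangeable. For a patient with Day 2 but no later sample, the three-day mean does not exist. Two simple ways to proceed are to drop the patient or to average the days that are present. Dropping departs from ITT and, if slow responders leave, flatters the arm that loses them. Averaging scores the leaver on an early, small reduction and penalises that arm. The two errors run in opposite directions, so in a comparison of 25 per arm the choice between them could matter.

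The text gives some reason to expect dropping. In Table 2 the Day 4 viremia sample is drawn at 71–72 hr, and doses follow at 72, 83–84 and 96 hr. Anyone who withdraws before that draw cannot have taken drug on every day. If section 3.2.3 is read as a limit, it leaves out these patients, which sits poorly with ITT.

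Loss related to response is also possible on the protocol's own terms: section 3.2.3 lets the investigator withdraw patients for treatment failure or adverse events, and gastrointestinal effects of the drug are expected.

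**Working it through.** **1. The plan's own figure.** Section 6.1 states "To achieve 80% power to detect a difference of one log viremia reduction" with SD 1 log, and "a sample size of 14 for each group (28 total) is required for a 5% one-sided type I error". The t-test calculation gives 14 per group (13 by the normal approximation). For 25 per group, 0.7 log and SD 1, power is 78.7% (noncentral t) or 79.7% (normal). For 1 log and SD 1.4 it is 80.1% (t). The stated figures reproduce. The baseline for what follows is 79% power and 5% one-sided error.

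**2. Size of the averaging error.** Assume the reduction grows by *g* log per day and a leaver has Day 2 only. If Day 2 has mean *m*, the three-day mean is (*m* + *m*+*g* + *m*+2*g*)/3 = *m*+*g*. The leaver is scored *m*, a shortfall of *g*. With *k* random leavers among 25, the arm mean falls by (*k*/25) × *g*. For *g* from 0.5 to 1.0:

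- *k* = 1: 0.04 × *g* = 0.02 to 0.04 log
- *k* = 2: 0.08 × *g* = 0.04 to 0.08 log
- *k* = 4: 0.16 × *g* = 0.08 to 0.16 log, so a true 0.70 becomes 0.62 to 0.54

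**3. Effect on the test.** Simulation with 25 per arm, SD of the three-day mean 1 log, within-patient correlation 0.6, *g* from 0.5 to 1.0, and leavers with Day 2 only. Except for 25 per arm and the SD of 1 log, these inputs are assumptions; the protocol gives none.

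| Leavers, one arm only | Average available days | Drop the patient |
|---|---|---|
| 2 celgosivir, random, true 0.70 | power 74–67% | little changed |
| 4 celgosivir, random, true 0.70 | power 68–55% | 0.70 log, power 75% |
| 1 placebo, random, no effect | false positives 5.8–6.7% | about 5% |
| 2 placebo, random, no effect | 6–8% | about 5% |
| 4 placebo, random, no effect | 8–13% | 5.3% |
| 2 celgosivir, slower half on Day 2, no effect | understates the drug | 7–8% |
| 4 celgosivir, slower half on Day 2, no effect | −0.12 to −0.20 log | +0.13 log, about 11% |

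In the last row the likelihood repeated-measures estimate stayed at 0.00, with SE about 0.29 against 0.28 for complete data.

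**4. When each route is biased.** A second simulation with other assumed inputs: placebo means 0.5, 1.5 and 2.5 log, correlation 0.7, SD of the three-day mean 1 log, Day 4 the missing day, and a constant effect of 0.70 unless stated. Monte Carlo error is about 0.008.

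| Missing Day 4 | All data | Drop | Average | Model |
|---|---|---|---|---|
| None | 0.693 | 0.693 | 0.693 | 0.693 |
| 20% in both arms, unrelated to outcome | 0.704 | 0.697 | 0.706 | 0.702 |
| Same, effect rising over days | 0.700 | 0.708 | 0.664 | 0.699 |
| 30% v 10%, unrelated to outcome | 0.685 | 0.687 | 0.590 | 0.687 |
| Celgosivir only, depends on Day 3 value | 0.694 | 0.877 | 0.584 | 0.695 |
| Celgosivir only, depends on unseen Day 4 value | 0.688 | 0.867 | 0.606 | 0.719 |

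Dropping is biased only where loss depends on outcome. Averaging is biased where loss differs by arm or where the effect changes over days. The model follows the full-data value except in the last row, where it is off by about 0.03 (0.719 − 0.688).

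**The case against.** The strongest reply is that this is missing-data handling, which a protocol may leave to its SAP. A per-patient mean with a t-test is a valid summary-measure analysis and is compatible with imputation, so dropping and averaging are not the only routes. That stands: the absence of a missing-value rule is not itself an error, and the text does not state either route. What remains is that section 6.2 does fix the estimator, and that section 3.2.3 already says something about who counts, in a way that does not fit ITT.

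A reader might infer that any missing day biases the comparison. The tables do not support that. Dropping four random leavers leaves 0.70 log and costs only power (75%). With two random leavers in each arm and no drug effect, false positives were 4.6% by averaging and 5.1% by dropping.

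A reader might also infer that the model is always unbiased. It needs missing at random, and it too leaves out a patient with no post-baseline value.

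Nor does the 30% dropout figure in section 5.6 show that the plan expects or accepts such loss. It is a trigger for terminating the study, not a forecast, and it is not specific to Days 2 to 4.

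Finally, gaps should be few. The samples fall at 23–24, 47–48 and 71–72 hr, all in hospital. Inclusion requires willingness to stay to Day 5, and patients who stop drug are asked to remain on schedule. Losing four patients from one arm and none from the other is an extreme case.

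**Conclusion.** The point holds in a limited form. The planned primary analysis has no value for an ITT patient who lacks one of three daily samples, and section 3.2.3 pulls against the ITT basis. Bias in the arm comparison is conditional. For averaging it takes unequal loss, or an effect that changes over the days. For dropping it takes loss related to response, and the two routes then err in opposite directions.

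The likely size is modest. One or two leavers in one arm move false positives from 5% to about 6–8% (by averaging if placebo patients leave, by dropping if slow celgosivir responders leave). With available-day averaging and leavers on celgosivir, power for 0.7 log falls from 79% to about 67–77%. These figures rest on assumed growth of 0.5 to 1.0 log per day, correlation 0.6 and leavers with Day 2 only. The protocol gives no missing-data rate, so they are illustrative. The change is worth making because it costs little and leaves the complete-data estimate as it is, not because a large distortion is expected.

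**What to change.** In section 6.2, make the primary virological analysis a mixed model for repeated measures on the Day 2, 3 and 4 log reductions. Use treatment, day and treatment-by-day, unstructured covariance and Kenward-Roger degrees of freedom. Define the estimate as the equal-weight average of the three daily treatment differences, tested at the level now planned. Include every randomized patient with at least one of the three values. Keep the t-test on the three-day mean as a sensitivity analysis, and say there how an incomplete mean is handled. In the same edit, reconcile the sentence in section 3.2.3 on who enters the effectiveness analysis with the ITT basis in section 6.2.

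The cost is a few sentences in the protocol and matching SAP text before unblinding, with standard SAS code and no new data or patients. The downsides are slightly more modelling, a missing-at-random assumption, and no recovery of patients without any post-baseline value.

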# Objectives and hypotheses

## Primary objectives

To investigate the effectiveness of celgosivir for treating acute dengue fever in adult patients

1. Hypothesis: The mean of virological log reduction (VLR) at Day 2, Day 3 and Day 4 will be greater for patients taking celgosivir than for those taking placebo (virological endpoint)
2. Hypothesis: The AUC above baseline of the fever curve for patients taking celgosivir will be lower than for those taking placebo (clinical endpoint)

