# Study Design

## Summary

This is a randomized, double blind, placebo-controlled, Phase 1b clinical study of celgosivir in adults age 21 to 60 with fever 38C of 48 hr duration, who meet at least two criteria indicating probable dengue infection, and who test positive for dengue infection by a point of care NS1 strip assay. Patients meeting all inclusion and exclusion criteria will be enrolled and admitted to the Investigational Medicine Unit (IMU).

Table 1 Study Design

| Cohort | N | Dose | Key Inclusion Criteria | Primary Outcome | Secondary Outcomes | Exploratory Outcomes |
| --- | --- | --- | --- | --- | --- | --- |
| 1 | 25 | Placebo | • Fever ≥38°C of ≤48 hr duration | • Viremia (laboratory) | • Safety & tolerability & PK |  |
| • Time to viral clearance | • Immuno-profiling |
| • positive NS1 strip assay | • NS1 | • Usage of analgesics |
| 2 | 25 | 400 mg loading dose then 200 mg q12hr | • 2 symptoms of probable dengue infection | • Fever (clinical) | • Leukocyte & Platelet count, Hemocon-centration | • Duration & magnitude of symptoms |
|

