Serum or plasma samples for viremia, quantitative NS1, immunological profile, DNA and RNA analysis, and PK will be transferred to Duke-NUS, Singapore Immunology Network, National University of Singapore or other laboratories for analysis and/or storage. The period of storage will not exceed 5 years.

After all study assessments have been completed on all patients and the database is locked, unblinding will occur. The primary virological endpoint will be the mean of virological log reduction (VLR) Study Day 2 to 4 between placebo and study drug groups. The primary clinical endpoint will be a reduction in fever AUC above baseline. Secondary endpoints for antiviral activity will be time to viral clearance, serum NS1 levels, leukocyte and platelet count, and hemoconcentration.

Secondary endpoints for assessing safety and tolerability are the number and severity of all adverse events and severe adverse events related to study drug compared to placebo using the 2009 WHO classification for grading adverse drug events. In addition, eight (8) samples for celgosivir serum concentrations will be obtained for population PK analysis.

Exploratory endpoints will be concentrations of various cytokines between placebo and treated groups, and changes in RNA expression of immunomodulatory genes. The trial will also assess the validity of the VASP and concomitant usage of analgesics between placebo and treatment groups as other measures of drug activity.

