## Selection and Withdrawal of Patients

### Inclusion Criteria

1. Male or female, age 21-65 years
2. Fever of  38C (directly measured or patient reported) of  48 hr duration.
3. At least two of the following criteria indicating probable dengue infection:
   1. Live or work in or recent travel to dengue endemic area
   2. Nausea and vomiting
   3. Presence of rash
   4. Aches and pains, including headache, or retro-orbital, muscle or joint pain
4. Positive NS1 strip assay or PCR
5. Able and willing to give written or oral informed consent
6. Willing to be an inpatient for from Study Day 1 to 5, and to return to the IMU on Study Days 7, 10, and 15.
7. Willing to keep a diary of pain medication usage and side effects

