## Concomitant Medications

Patients may continue their baseline medication(s). Patients may be administered paracetamol according to the Principal Investigator’s or Co-investigators’ instructions. The daily dose of all medications should be recorded on the appropriate pages of the CRF.

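### Fever AUC is measured above each patient's own, usually febrile, entry temperature, which substantially reduces the sensitivity of the primary clinical endpoint to faster defervescence

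*Protocol*

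**What the plan says.** Section 2.1 states the clinical hypothesis: "The AUC above baseline of the fever curve for patients taking celgosivir will be lower than for those taking placebo". Section 3.1 repeats the definition: "The primary clinical endpoint will be a reduction in fever AUC above baseline".

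Section 6.2 supplies the computation. Temperature is taken in each patient at baseline and through Day 5 and plotted as a curve. Then: "The area under this curve but above the baseline value will be computed for each patient". The arms are compared by a two-sample, one-sided t-test.

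The appendix schedule (Table 2) places screening and baseline between 14 h and 0 h before the first dose, and its note b sets temperature monitoring every 2 hours. Table 1 in section 3.1 gives the entry requirement as "Fever ≥38°C of ≤48 hr duration". Section 3.2.1 adds that this fever may be "directly measured or patient reported". Nowhere is baseline defined as a normal, afebrile or pre-illness temperature.

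**The concern.** The reference line is a reading taken while most patients are ill. Area above it records only how far and how long a patient becomes hotter than at entry. A drug that shortens fever acts mainly on the time spent febrile but cooler than at entry, and the definition gives that time no weight.

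The reference also varies by patient. Someone whose reading happens to be near normal, having qualified on reported fever, has nearly all later fever counted. Someone read at a peak has almost none counted. That spread has nothing to do with treatment, and it enters the variance of the t-test.

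This is one of two primary endpoints and the only clinical one. If the trial shows no difference on it, the reader cannot tell an inactive drug from an insensitive measure.

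**Working it through.** **The plan's own figures.** Section 6.1 sizes the trial on viremia only: 14 per group for 1 log at SD 1 log, one-sided 5%, 80% power; and 0.7 log detectable with 25 per group. The noncentral t gives 82.4% power at 14 per group (79.7% at 13) and 78.7% for 0.7 log at 25 per group, so both figures reproduce. No power figure is given for fever.

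**Definitions compared.** With *T(t)* the temperature at *t* hours and *T(0)* the baseline reading:
- as written: area = ∫ max(*T(t)* − *T(0)*, 0) d*t*
- fixed reference *c*: area = ∫ max(*T(t)* − *c*, 0) d*t*

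The window used is 0–96 h, the dosing phase in Table 2. The value *c* = 37.5°C is for illustration only.

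**Steady fall.** If temperature falls linearly from *T(0)* to 37°C over *h* hours, *T(t)* never exceeds *T(0)*, so the first area is exactly 0 for every *h*. The second is (*T(0)* − *c*)² × *h* / [2 × (*T(0)* − 37)].

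| Entry | Hours to 37°C | Above own baseline | Above 37.5°C |
|---|---|---|---|
| 38.5°C | 36 | 0 | 1² × 36 / 3 = 12 °C·h |
| 38.5°C | 72 | 0 | 1² × 72 / 3 = 24 °C·h |
| 40°C | 72 | 0 | 2.5² × 72 / 6 = 75 °C·h |

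**Dependence on the baseline reading.** Take one assumed course: a linear fall from 39°C to 37°C with a daily swing of amplitude 0.5°C that shrinks as fever resolves. Score it against different recorded baselines:

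| Recorded baseline | Fever gone at 48 h | Fever gone at 72 h |
|---|---|---|
| 37.5°C | 29.3 °C·h | 42.5 °C·h |
| 38°C | 13.4 | 20.8 |
| 39°C | 1.2 | 1.9 |
| 39.5°C | 0 | 0 |

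**Power by simulation**, 25 per arm, one-sided 5% t-test. All curve parameters are assumptions.

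*First set* (1,500 trials): entry excess over 37°C mean 1.5, SD 0.5; defervescence midpoint SD 20 h; daily amplitude 0.35°C; autocorrelated noise SD 0.35°C.
- Midpoint 60 h against 36 h: about 40% power with own baseline, 81% with 37.5°C.
- Midpoint 60 h against 42 h: 27% against 60%.
- Correlation of the own-baseline area with entry temperature: about −0.57.

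*Second set* (4,000 trials per scenario): mean defervescence at 72 h against 48 h, SD 18 h.

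| Mean starting fever, initial plateau, daily amplitude, noise SD | Mean area above own baseline (48 h vs 72 h) | Power, own baseline | Power, 37.5°C |
|---|---|---|---|
| 39°C, none, 0.5, 0.3 | 2.3 vs 3.6 °C·h | 24% | 80% |
| 39°C, 24 h, 0.5, 0.3 | 7.5 vs 8.6 | 12% | 54% |
| 38.3°C, 24 h, 0.5, 0.3 | 8.5 vs 10.1 | 12% | 33% |

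Across all six scenarios run, power was 12–25% with own baseline and 33–80% with 37.5°C.

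**The case against.** **Baseline may have been meant as normal temperature.** The text does not say so. Section 6.2 treats it as a measurement made in each patient. Where the protocol wants a different reference it names one: hemoconcentration is set against the Day 15 hematocrit. If a normal value was intended, the same sentences need correcting.

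**The SAP will settle it.** Section 6.2 does promise a detailed SAP, and the integration rule and exact window belong there. The reference line is different, because the protocol already fixes it in three places. An SAP that follows the protocol inherits the problem; one that departs from it changes a primary endpoint.

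**The zeros depend on a steady fall.** This stands. Plateaus, daily swings and later rises give positive scores, and the simulated arms do separate somewhat. A reader might infer that faster defervescence cannot be detected at all; the power figures above show reduced sensitivity, not none. Nor does a patient entering at 40°C necessarily score zero: any later time above 40°C counts, and entry within 48 h of onset does not exclude a further rise.

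**Not every baseline will be febrile.** This also stands, because reported fever qualifies. It does not rescue the endpoint, since the reference then differs between patients. A reader might add that paracetamol lowers baseline readings. Section 4.4 says only "Patients may be administered paracetamol" and nothing about use before the reading, so that remains inference.

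**Randomisation protects the comparison.** It does. Individual patients can be ranked against their true fever burden, and a reader might infer that the treatment comparison is therefore biased. It is not: entry temperature is balanced in expectation, and a simulation with no treatment effect rejected about 5% of the time.

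**Conclusion.** The point holds as a loss of sensitivity and interpretability in a primary endpoint, not as a source of bias or type I error inflation. That a steadily resolving fever scores zero for a patient febrile at the baseline reading follows from the wording alone.

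The size rests on assumed curves. Power falls to about half in the first set (40/81 = 0.49; 27/60 = 0.45) and to less than half in the second (24/80 = 0.30; 12/33 = 0.36). The direction is consistent, but the values are illustrative because the protocol gives no fever course.

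The score depends strongly on the entry reading. It would go too far to say that it mostly measures that reading: a correlation of −0.57 explains 0.57² = 0.32, about a third, of the variance.

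**What to change.** Before unblinding, amend sections 2.1, 3.1 and 6.2 together. Define fever AUC as the area of the temperature curve above one fixed afebrile reference temperature, the same for all patients and chosen by the clinical team. Compute it from the scheduled 2-hourly readings over a common window.

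Preferably compare the arms with baseline temperature as a covariate. That is a recommendation rather than part of the correction. The integration rule and exact window can go in the SAP.

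The cost is a protocol amendment that redefines a primary endpoint and so changes what the trial tests. No new data are needed.
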